A final follow-up will be conducted via telephone and postal questionnaires (EQ-5D, the OAK test, TABS and the disease-specific Duke Anticoagulation Satisfaction Scale (DASS)) [50] approximately 90 days post-discharge. Corroboration of details of any adverse events experienced by the patient and their current medications and INR results will be requested from their GP at this time via a postal form. Non-responders will receive a reminder telephone call or fax after 4 to 8 weeks. For patients experiencing readmission to hospital during their 90 days post-discharge, Australian Refined Diagnosis Related Group (AR-DRG) codes and other details will be obtained from their notes from the relevant hospital's Medical Records Department. The data to be collected at each time point are summarised in Table 3.

**Table 3 T3:** Data collection summary

Data	Time point				
	
	Baseline	Visit 1	Visit 2*	Visit 3^i ^or Day 8^c^	Day 90
Demographics, alcohol intake, smoking history, drug history, height, weight, serum creatinine, haematocrit	✓				

Warfarin therapy details- indication, intended duration, target INR, newly commenced or continuing, heparin pre-treatment, inpatient doses/INRs, doses/INR on discharge, warfarin counselling documented	✓				

Medications, warfarin drug interactions	✓			✓	✓

Medical history	✓				

INR	✓	✓**	✓**	✓**	✓

Warfarin dosing/INR history	✓			✓	✓

Number of GP consultations (since discharge, or between Days 8 and 90)				✓	✓

Adverse events, hospital readmissions				✓	✓

Warfarin continuing, reason for discontinuation		✓	✓	✓	✓

Beyth Bleeding Risk score	✓^C^	✓^I^			

Warfarin dose, changes recommended, visit outcome, visit length, travel time		✓	✓	✓	

QoL (EQ-5D), warfarin knowledge		✓		✓	✓

QoL (Duke Anticoagulation Satisfaction Scale (DASS))					✓

Adherence (Tool for Adherence Behaviour Screening (TABS))				✓	✓

Self-reported health services utilisation					✓

(* Visit 2 if required, ** POC monitoring, ^C ^Control, ^I ^Intervention)

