Based on an assessment of the patient's bleeding risk, the GP and accredited pharmacist will collaboratively determine whether the patient will receive 1 (the 'Level 1 Service') or 2 (the 'Level 2 Service') subsequent visits. This risk assessment will be based on calculation of their Beyth Outpatient Bleeding Risk Index (which estimates a patient's risk of major bleeding within 3 and 12 months) [51], INR stability and an overall evaluation encompassing falls risk and drug interaction potential. A previously utilised definition of stability will be utilised: "2 consecutive INR results within the target range or the first measurement in the therapeutic range when the previous or subsequent INR varied by no more than 0.5 INR units outside the target range" [52]. Only patients deemed to be at 'low' or 'intermediate' risk based on the Beyth Outpatient Bleeding Risk Index and with no other risk factors will be candidates for the Level 1 Service. All other patients - those at 'high' risk on the Beyth Outpatient Bleeding Risk Index (due to their high estimated major bleeding risk, or with additional risk factors, as detailed above), will be mandated to receive the Level 2 Service.

## Visits 2 and 3

Visits 2 and 3 will provide opportunities for POC INR monitoring, provision of warfarin education and resolution of any detected drug-related problems. If patients require more frequent INR tests than the service can offer, pathology testing in combination with POC INR testing will be permitted.

At Visit 3, the completion of the service, data will be collected, the TABS survey administered and the EQ-5D questionnaire and OAK test re-administered. The accredited pharmacist will forward a copy of their HMR report and the standard handover document to the patient's GP and community pharmacy. A similar handover document will be given to the patient.

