### Outcome measures

The primary outcome measure will be the proportion of patients experiencing a major bleeding event in the 90 days after hospital discharge. Major bleeding will be defined using the previously accepted definition of:

*"fatal bleeding, and/or symptomatic bleeding in a critical area or organ (especially intracranial or retroperitoneal), and/or bleeding causing a fall in haemoglobin level of 2 g/dL or more, or leading to transfusion of two or more units of whole blood or red cells" *[53].

Secondary outcome measures will be the combined incidence of major bleeding and thromboembolic events, death, cessation of warfarin therapy, INR control at 8 days post-discharge and unplanned hospital readmissions from any cause. INR control will be calculated based on the patient's individual target INR range, and defined as such as within this range ('therapeutic'), below the range ('subtherapeutic') or above the range ('supratherapeutic'). Rates of INRs greater than 4 will also be investigated as this confers a markedly increased risk of intracranial haemorrhage [54].

Other outcomes will include INR control to Day 90, QoL, warfarin knowledge, other adverse events (including minor bleeding) and adherence. Minor bleeding will be defined as bleeding requiring health professional consultation, but not hospitalisation, to ensure consistency and minimise the risk of recall bias. The EQ-5D utility score for QoL will be calculated using the United Kingdom Time Trade-Off data set, as has been reported previously [47]. No Australasian data set is currently available. Time in therapeutic INR range will be calculated using Rosendaal's linear interpolation method [55]. Warfarin drug interaction severity ratings will be classified as 'Severe', 'Moderate', 'Caution', 'Minor' and 'Nil' using the eMIMS database [56], while medical history will be based on the International Classification of Diseases 10 coding system (ICD-10) [57].

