### Statistical analysis

Demographic data will be utilised to compare the control and intervention groups for a range of parameters (e.g. age, gender, PhARIA class, living and medication management arrangements, co-morbidities, warfarin drug interactions) using independent samples t-testing for continuous data and chi-squared analysis for categorical data. Outcome data will be reported using parametric statistics, with independent samples t-testing utilised for the majority of continuous variables and chi-squared analysis for the majority of discrete variables. Data will be statistically analysed across the 3 groups (control, Level 1 Service, and Level 2 Service). For the evaluation questionnaires, responses will be recorded on modified Likert scales, with 0 representing "Strongly agree" and 10 "Strongly disagree". Qualitative feedback will obtained via open-ended questions. Data analysis will involve descriptive statistics and thematic analysis of the qualitative responses.

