The trial faces several potential challenges, including the necessity for an expedited GP consent/HMR referral process to ensure that the first home visit occurs within 2 to 3 days post-discharge. Previous work in this area at the Royal Adelaide Hospital has achieved post-discharge HMRs within 6.5 days post-discharge, varying from 3.9 to 8.1 days depending on slight variations in the model [65]. The time to the conduct of a post-discharge HMR can be as long as 18 [66] or 32 days [67]. The timeliness of the HMR is particularly important, not only because of the requirement for INR monitoring, but also because post-discharge medication reviews are best conducted soon after discharge (some authors recommend within 1 week)[65] to best enable opportunities to enhance medication adherence, improve medication related knowledge and identify medication-related problems (as the probability of medication misadventure is recognised as being highest during the 10 day post-discharge period) [68]. As discussed, processes have been implemented to address this and other potential challenges as completely as possible during the study planning stage using learnings from the previous trial. The study's other strengths lie in a strong multidisciplinary team and the use of an existing referral and funding structure.

Based on the excellent results of the previously trialled program [36], this service has been proposed as a potential solution to many of the issues faced in the post-discharge period by patients taking warfarin. The aim is to incorporate POC INR monitoring and warfarin education into the existing HMR remuneration structure to produce a streamlined and sustainable model more pragmatic for widespread implementation into practice. It is hoped that this study will provide the evidence to support the national roll-out of the program as a new professional community pharmacy service.

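### Service level is assigned at Visit 1 but bleeding is counted from discharge, so enrolled intervention patients who are never visited have no place in the stated three-group comparison

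*Protocol article*

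**What the plan says.** All references are to the protocol article.

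- **Outcome clock.** Outcome measures defines the primary outcome as "the proportion of patients experiencing a major bleeding event in the 90 days after hospital discharge".
- **Controls.** Control patients are approached and give consent before discharge, so their group is known when the clock starts (Control patients).
- **Intervention patients.** They are recruited in hospital in the same way, but no level exists yet. Under Visit 1, "the GP and accredited pharmacist will collaboratively determine whether the patient will receive 1 (the 'Level 1 Service" or two further visits. The decision rests on a risk assessment: "Only patients deemed to be at 'low' or 'intermediate' risk based on the Beyth Outpatient Bleeding Risk Index" and without other risk factors can be Level 1. Table 4 puts Visit 1 at 2-3 days after discharge. In Table 3 the "Beyth Bleeding Risk score" is recorded at baseline for controls and at Visit 1 for intervention patients.
- **Analysis groups.** Statistical analysis states "Data will be statistically analysed across the 3 groups (control, Level 1 Service, and Level 2 Service". The Overview describes the comparison as one between patients who receive the service and patients under usual care.
- **Delay.** The Discussion notes that earlier work at one of the study hospitals "has achieved post-discharge HMRs within 6.5 days post-discharge, varying from 3.9 to 8.1 days", and that intervals of 18 or 32 days are reported elsewhere.

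**The concern.** Two of the three analysis groups are defined by something that happens after the outcome period has begun. A control who bleeds or dies on day 1 is in the control group. An intervention patient with the same event who is then never visited has no level and so no group. This is the structure behind immortal-time bias: membership of Level 1 or Level 2 requires having reached the assessment.

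Two things are at stake. Early events can be removed from one side only. Failed referrals also disappear from the result, although the Discussion justifies the design by its focus on translation into practice, for which failure to deliver the visit is itself a finding.

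**Working it through.** **The plan's own figures.** The article gives no figure for this point. Its sample size of about 108 per group (10% versus 2%, 80% power, p = 0.05) is reproduced by the standard two-proportion formula, one-sided and without continuity correction; the two-sided version gives 138. The point does not depend on that calculation. Only the 10% usual-care risk and the targets of 160 control and 240 intervention patients are taken from it.

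**Step 1: who has no group.** Setting the sections side by side:

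| Patient | Group in the three-way analysis |
|---|---|
| Control, event on day 1 | Control |
| Intervention, event on day 1, later visited | Level 1 or Level 2 |
| Intervention, event on day 1, never visited | None |
| Intervention, no event, referral fails | None |

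**Step 2: direction.** Let p be the 90-day risk in all enrolled intervention patients, u the share never visited and q the risk among them. The risk in those left is (p - uq)/(1 - u). This is below p when q > p and above p when q < p. Dropping patients because of an early bleed (q = 1) favours the service. Dropping event-free failed referrals (q = 0) works against it. The net direction depends on the mix.

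**Step 3: upper bound for lost early bleeds.** Assume no true effect, p = 0.10 in every group, a share s of 90-day bleeds before Visit 1, and that every such patient is lost. Then u = ps and q = 1, so the observed risk is p(1 - s)/(1 - ps). Expected bleeds lost are 240 × 0.10 × s = 24s.

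Under uniform risk, s = (day of Visit 1)/90:

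- Day 2.5: s = 0.0278; 24s = 0.67 bleeds; risk = 0.09722/0.99722 = 0.09749; risk ratio 0.9749, about 0.97.
- Day 6.5: s = 0.0722; 24s = 1.73 bleeds; risk = 0.09278/0.99278 = 0.09345; risk ratio 0.9345, about 0.93.
- Day 8.1: s = 0.090; 24s = 2.16 bleeds; risk = 0.0910/0.9910 = 0.0918; risk ratio 0.92.

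As a sensitivity case, assume half of all 90-day bleeds fall evenly in the first 10 days, so s = 0.5 × day/10. The article does not state this.

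- Day 3: s = 0.15; 3.6 bleeds; risk 0.0863; risk ratio 0.86.
- Day 6.5: s = 0.325; 7.8 bleeds; risk 0.0698; risk ratio 0.70.

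**Step 4: false findings in favour of the service.** Exact enumeration of the uncorrected chi-squared test, two-sided 5%, with 160 versus 240 and no true effect, gives 2.7% with nothing lost. With early bleeds lost it gives:

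| Visit 1 | Uniform risk | Front-loaded (assumed) |
|---|---|---|
| Day 3 | 3.3% | 7.1% |
| Day 6.5 | 4.3% | 19% |

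**The case against.** The strongest reply is that exclusion is inferred. No sentence says unvisited patients are dropped, the three groups appear in one condensed line, and a full analysis plan not shown here may assign these patients. A pooled intervention group also exists in the article: the target of 240, the baseline comparison of control with intervention, and an abstract that contrasts service patients with controls. Day-90 follow-up of intervention patients is not made conditional on Visit 1.

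Part of this stands. A reader might infer that the protocol excludes these patients by rule; it does not. But the point does not rest on a missing detail. The grouping the article does state is defined after time zero. The pooled group serves recruitment targets and baseline characteristics, and the Overview's outcome comparison is worded around patients receiving the service. A plan that followed this text would carry the problem forward.

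The second reply is that late visits belong to earlier programmes, and this trial has telephone GP consent and pre-populated referral forms to avoid them. That is fair: the 6.5-day figure is a warning, not a forecast. Visit 1 still depends on the GP, the community pharmacy and an accredited pharmacist acting in sequence, and the Discussion itself names the timing as a challenge.

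The third reply is that the effect is trivial if visits are punctual. Under uniform risk that is correct: fewer than one expected bleed in 240 patients, against a planned contrast of 10% versus 2%.

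**Conclusion.** The point holds as a defect in how the comparison is defined. The article's three groups give no place to enrolled intervention patients who are never visited, while controls with the same early course are counted.

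The size is modest on the article's own schedule: a risk ratio of about 0.97 at day 2.5 and 0.93 at day 6.5. Both are upper bounds that assume 10% risk, no true effect, uniform risk and loss of every early bleed. Lower ratios need front-loaded bleeding. A reader might take that from the Discussion, but its 10-day statement concerns medication misadventure, and the Background compares the first month of therapy with the period after the first year. Neither gives the share of major bleeds in the first days.

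Two other stronger readings are not supported. Not every early bleeder is lost, because those still visited receive a level. Nor does the bias always favour the service, because event-free failed referrals can shift the estimate the other way.

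**What to change.** - **Primary comparison.** State it as control versus all consented, discharged intervention patients, followed from discharge whether or not a referral or any visit took place.
- **Follow-up.** Complete Day-90 follow-up for intervention patients who were not visited. This has to be arranged prospectively.
- **Reporting.** Give the number and proportion never visited, with reasons.
- **Level-specific results.** Treat them as secondary and descriptive, since level is chosen by bleeding risk. If a level is compared with control, use a common landmark no earlier than the time by which levels have actually been assigned, for example the end of the Table 4 visit window at day 10, and exclude earlier events in all groups. A day-3 landmark is not enough: if Visit 1 comes later, the same problem remains between day 3 and the visit.

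The cost is a change of analysis wording, a little extra follow-up, and an estimate that may be more conservative. The landmark analysis also answers a narrower question, about bleeding after the landmark only, which is a further reason to keep it secondary.

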**Methods/Design:**

The service will be trialled in 8 sites across 3 Australian states using a prospective, controlled cohort study design. Patients discharged from hospital taking warfarin will receive 2 or 3 home visits by a trained 'home medicines review (HMR)-accredited' pharmacist in their 8 to 10 days after hospital discharge. Visits will involve a HMR, comprehensive warfarin education, and POC INR monitoring in collaboration with patients' general practitioners (GPs) and community pharmacists. Patient outcomes will be compared to those in a control, or 'usual care', group. The primary outcome measure will be the proportion of patients experiencing a major bleeding event in the 90 days after discharge. Secondary outcome measures will include combined major bleeding and thromboembolic events, death, cessation of warfarin therapy, INR control at 8 days post-discharge and unplanned hospital readmissions from any cause. Stakeholder satisfaction will be assessed using structured postal questionnaire mailed to patients, GPs, community pharmacists and accredited pharmacists at the completion of their study involvement.

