### Sample size

Based on sample size calculations, groups comprising approximately 120 patients in each (control, 2-visit model, and 3-visit model) are estimated as being statistically adequate. This is based on the previous RCT of this model of care where 10% of the usual care group experienced a major bleeding event within 90 days post-discharge, which was reduced to 2% in the intervention group [36]. Using these figures, approximately 108 patients are needed per group at a power of 80% and p = 0.05. Published data are also available indicating that approximately 30-40% of patients commenced on warfarin experience a bleeding complication within 3 months [16,18,36,45]. The aim of the intervention program is to reduce this figure to below 10%, in which case approximately 72 patients are needed per group at a power of 80% and p = 0.05. The proposed recruitment targets are thus 160 in the control group and 240 in the intervention group (120 receiving the 2-visit model and 120 the 3-visit model).

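### The protocol asks whether the service beats usual care but analyses outcomes across three groups, two of them formed by bleeding risk, and names no primary contrast

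*Protocol article*

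**What the plan says.** The question is put as a two-group comparison. The abstract (Methods/Design) says "Patient outcomes will be compared to those in a control, or 'usual care', group", and the Overview likewise sets patients receiving the service against patients receiving usual care. The endpoint is binary: "The primary outcome measure will be the proportion of patients experiencing a major bleeding event in the 90 days after hospital discharge" (Outcome measures).

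The Sample size section first plans three groups of about 120 (control, 2-visit, 3-visit). It applies a two-group calculation to the finding that "10% of the usual care group experienced a major bleeding event within 90 days post-discharge, which was reduced to 2% in the intervention group", and then concludes "The proposed recruitment targets are thus 160 in the control group and 240 in the intervention group", with the 240 divided as 120 and 120.

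The Statistical analysis section uses the control-versus-intervention comparison for demographic data. For outcomes it says "Outcome data will be reported using parametric statistics, with independent samples t-testing utilised" for most continuous variables, with chi-squared analysis for most discrete ones, followed by "Data will be statistically analysed across the 3 groups" (control, Level 1 Service, Level 2 Service). No contrast is called primary.

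Under Visit 1, the general practitioner and accredited pharmacist choose the level from the Beyth index, INR stability and an overall evaluation that includes falls risk and drug interactions. Only low- or intermediate-risk patients without other risk factors are candidates for Level 1; all others go to Level 2. Controls are given no level.

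**The concern.** The two intervention groups are selected to differ in the risk of the primary outcome. Control versus Level 1 sets a mixed-risk group against a selected lower-risk group, and control versus Level 2 does the reverse. Without any service effect, Level 1 would tend to look protective and Level 2 harmful, and a 3x2 test would detect that spread. A significant three-group result would not tell the reader whether the service works.

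Because no contrast is named, a positive primary finding could also be claimed from any of several comparisons, including Level 1 versus Level 2, which is confounded by the risk rule. The results are meant to inform a national roll-out (Discussion), so the contrast that answers the question should be fixed before the data are seen.

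**Working it through.** **Inputs from the protocol.** Rates 10% and 2%; p = 0.05; power 80%; 160 control patients and 120 + 120 intervention patients; chi-squared for discrete outcomes. The low- and high-risk bleeding rates used in step 2 are assumptions, since the protocol gives none.

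**1. The plan's own figures.** The pooled-variance formula for two proportions is n = [z_α·√(2p̄q̄) + z_β·√(p₁q₁ + p₂q₂)]² / (p₁ − p₂)². With p̄ = 0.06, the two roots are √0.1128 = 0.3359 and √0.1096 = 0.3311.
- One-sided 0.05: (1.645 × 0.3359 + 0.842 × 0.3311)² / 0.0064 gives 108, matching "approximately 108 patients are needed per group at a power of 80% and p = 0.05".
- Two-sided 0.05: 1.960 replaces 1.645, and the answer is 138.
- The second figure, "approximately 72 patients are needed per group at a power of 80% and p = 0.05", is reproduced for 30% versus 10% by a two-sided test with continuity correction.

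Both are two-group calculations with undivided α. The difference in sidedness is a separate matter. It matters here only because the powers below are two-sided.

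**2. No service effect, levels formed by risk.** Overall rate 10%; controls are 80 low-risk and 80 high-risk patients; Level 1 is 120 low-risk; Level 2 is 120 high-risk; the service changes nothing. The approximate noncentrality of the 3x2 chi-squared test (2 df) is λ = Σ nᵢ(pᵢ − p̄)² / (p̄q̄), where the control term is zero.
- 7%/13%: λ = 2 × 120 × 0.03² / 0.09 = 2.4, so the chance of significance is about 26%.
- 5%/15%: λ = 2 × 120 × 0.05² / 0.09 = 6.67, so about 63%.

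Binomial simulation (1,000,000 trials per case), share of trials significant at 0.05:

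| Assumed low/high rates | 3x2 test | At least one level vs control | Pooled 240 vs 160 |
|---|---|---|---|
| 10%/10% | 4.9% | 9.7% | 4.8% |
| 7%/13% | 26% | 27% | 4.7% |
| 5%/15% | 64% | 56% | 4.5% |

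**3. Equal true rates, for reference.** With 160/120/120 patients and a common rate of 5% or 10%, three unadjusted pairwise chi-squared tests give at least one significant result in 12.0% or 12.7% of trials. The two control contrasts alone give 9.1% or 9.7%. A single 3x2 test gives 4.6% or 4.9%.

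**4. Power at 10% versus 2%, two-sided 0.05.** Power = Φ[(0.08 − 1.960·s₀) / s₁], where s₀ and s₁ are the standard errors under the null (pooled) and the alternative.
- Pooled, 160 vs 240: p̄ = (16 + 4.8)/400 = 0.052, s₀ = 0.02266, s₁ = 0.02538; Φ(1.40) = 92% (94% by simulation).
- One level, 160 vs 120: p̄ = (16 + 2.4)/280 = 0.0657, s₀ = 0.02992, s₁ = 0.02694; Φ(0.79) = 79%. With Bonferroni correction for two or three tests this falls to 68% or 62%.
- 3x2 test at 10%/2%/2%: 89% by simulation.

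**The case against.** A reader might infer that the primary outcome will be tested by three pairwise tests at 0.05 each, so that the error rate is about 12%. The protocol does not say this. The t-test, which does imply pairs, is named for continuous variables. The primary outcome is binary, and chi-squared across three groups may well be one 3x2 test, with about 5% error under equal rates and 89% power. The 12% and 79% figures hold only on a pairwise reading. How multiplicity is handled may also properly sit in an analysis plan that is not shown.

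A reader might also infer that the 240 versus 160 comparison has been given up. It has not: it appears in the abstract and Overview and underlies the recruitment targets. It is simply not named for outcomes. Nor does the risk rule guarantee that the groups differ, because the service could offset a difference in risk.

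Finally, the Objectives refer to two intensities of service, so reporting by level is a legitimate aim.

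All of this stands, and it limits the point. It does not remove it. The 3x2 test keeps its 5% error only if all three groups share one true rate, and the level-assignment rule makes that implausible. The three-group analysis is also stated in the text, so this is not a detail left for later.

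**Conclusion.** The concern holds in this form: the stated outcome analysis does not match the stated question, and no primary contrast resolves the mismatch. Under the assumed risk rates, a 3x2 test would be significant in about 26% to 64% of trials of a service with no effect, while the pooled test stays near 5%.

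The 26% to 64% range rests on three assumptions: the 7%/13% to 5%/15% rates, a 50:50 risk mix in both the control and the whole intervention group, and levels that follow risk exactly. A weaker link between level and bleeding risk would bring it down towards 5%. The pooled test's 5% requires the two groups to have the same case mix, which a non-randomised design does not ensure. The 92% power assumes 2% in both levels and an unadjusted test.

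**What to change.** - State one primary contrast: all intervention patients (240) versus all controls (160) on major bleeding within 90 days, two-sided 0.05.
- Report Level 1 and Level 2 results as secondary estimates with confidence intervals, preferably against controls in the same baseline bleeding-risk stratum. Table 3 already collects the Beyth score in both groups. It will not reproduce the level choice exactly, since INR stability and overall judgement also enter.
- For continuous outcomes, use a regression model in place of repeated two-sample t-tests over three groups.

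This changes analysis wording only and needs no extra patients or data. The price is that level-specific p-values lose any primary status. Pooling removes the selection between levels, but it does not remove confounding between the control and intervention groups, which still needs its own adjustment.
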